### Sample size calculation radiostereometric analysis

Sample size calculation for radiostereometric analysis (maximum total point motion of the glenoid component after 2 years will be used as primary radiostereometric analysis effect parameter) was performed with an expected standard deviation (SD) of 0.4 mm, a minimally clinically important difference of 0.4 mm, a significance level at 5% and power of 0.90 and resulted in 22 participants in each group (56 participants with allowance for 20% drop-out) [26]. There are no data metrics for migration of the glenoid component in reverse shoulder arthroplasty, but the sample size fits with estimates in previous studies comparing two different orthopaedic implants. The argument is that RSA has high accuracy and, therefore, that few patients are needed [12].

### Sample size calculation WOOS

The standard deviation of WOOS is set at 15 (15% of a maximum score). The minimally clinically important difference is set at 10 (10% of a maximum score), the significance level is set at 5% and the power of 0.90. With these assumptions, 48 patients are needed in each group resulting in a study population with 122 participants [26] (allowing for 20% drop-out). MCID of WOOS for patients with reverse shoulder arthroplasty for degeneration of the glenohumeral joint with either rotator cuff insufficiency or severe posterior glenoid wear has not been defined. Thus, the estimates used in the sample size calculation were based on studies which included patients with an anatomical total shoulder arthroplasty for osteoarthritis [27, 28].

## Discussion

This study aims to determine if DELTA Xtend Reverse Shoulder System Lateralized Glenosphere Line Extension has a better outcome than the Standard DELTA Xtend Reverse Shoulder System. The patients will be divided into two groups and equally randomized and treated. There is a possibility of being treated with what turns out to be an inferior arthroplasty. Today, it is not known if one treatment is better than the other as the two types of glenospheres are considered equal effective and safe.

Sirveaux et al. [4] reported that inferior scapular notching was associated with increased risk of revision, and Mollon et al. [5] described lower clinical outcomes for these patients. This study aims to explore metallic lateralization as a solution to prevent inferior scapular notching and subsequently better outcomes. Lateralization of the glenoid off-set has earlier been reported as the most efficient technique to avoid inferior scapular notching [8]. Furthermore, lateralization has been described to improve movement [9] but at the same time makes greater demands to the deltoid muscle [29]. There has also been reported a higher rate of loosening [8]. Implant migration can be the first sign of loosening. Radiostereometric analysis has been used to measure implant migration in numerous studies for more than 20 years [30], but this is, to our knowledge, the first time radiostereometric analysis is used to compare the outcome for conventional reverse shoulder arthroplasty and lateralized reverse shoulder arthroplasty in a randomized controlled trial. DXA has been used in shoulder patients before.

The model-based radiostereometric analysis technique is less precise than the marker-based method. However, precision error values are still acceptable for clinical studies aimed at evaluating implant migration [31]. The use of radiostereometric analysis for the evaluation of implant migration has been used frequently in the evaluation of hip and knee arthroplasty surgery. It has been shown that the late revision due to aseptic loosening of the tibial component in total knee arthroplasty is consistent with early radiostereometric analysis findings of continuous migration past the first postoperative year [32]. Therefore, it has been suggested that a small series of new arthroplasties should be monitored with radiostereometric analysis the first 2 years postoperatively, as part of a safe phased introduction of new arthroplasties [30, 33, 34].

The standard follow-up time after a shoulder arthroplasty at our department is 3 months. The patients included in this study will additionally be examined within 1 week and at 6, 12 and 24 months. This can both contribute to the patients feeling more secure by handling problems as they come or entail a long-lasting feeling of being ill and furthermore being time-consuming. The patients will not be financially compensated for the extra visits.

As part of safe implementation of a new orthopaedic surgical product [35], after being tested by the manufacturer, this study will test the lateralized glenosphere with radiostereometric analysis and a RCT study. If it finds an advantage without infection as an expense, it can be implemented in the treatment of patients without further testing. The treatment will be controlled through the Danish Shoulder Arthroplasty Registry [36, 37].

The study aims to earn knowledge of the treatment option with the most optimal outcome for future patients needing a reverse shoulder arthroplasty.

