## Methods and design

### Study design

This study is an investigator initiated, single-centre, 1:1 randomized controlled trial, which will compare the DELTA Xtend® Reverse Shoulder Lateralized Glenosphere Line Extension (intervention group) with the standard DELTA Xtend® Reverse Shoulder System (control group). The two implants are produced by Depuy Synthes (Raynham, MA, USA). The SPIRIT reporting guidelines [20] and checklist (Additional file 1: Appendix 1) were used.

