#### Secondary functional outcomes

*Constant-Murley Score*: The Constant-Murley Score includes an evaluation of pain, range of motion, activities of daily living and strength. The maximum score for the evaluation of pain and activities of daily living is 35 points. For the objective evaluation, there is a maximum score of 65 points, of which 40 are from a range of motion and 25 are from strength. Thereby there is a collected maximum of 100 points, which indicates a shoulder without any disabilities. The difference in mean score between the preoperative score and the 2-year follow-up score is the primary value of interest. In this study, a Danish version [22] of the modified Constant score [23] is used.

*Oxford Shoulder Score (OSS)*: The OSS was invented as a measurement tool to assess function and pain after elective shoulder surgery [24]. It contains 12 questions with a score from 0 to 4. The total score ranges from 0 to 48, with 48 as the best score. The scores are converted into a percentage of the maximum score to ease the interpretation. The difference in mean score between the preoperative score and the 2-year follow-up score is the primary value of interest. In this study, the Danish version, which has been translated and validated with the classical test theory [25], of OSS is used.

*Complications and side effects*: Any incident of medical (cardiovascular, embolism, pneumonia) and surgical complications (nerve damage, fracture, infection, instability, disposition of component and dislocation) will be noted, as well as revision surgery (removal or exchange of any component).

*Pain and patient satisfaction*: Pain is evaluated on the day of examination with the VAS score with scores from 0 to 10, with 10 points as the worst possible pain. The patients will describe the outcome on a 7-point scale, with ‘much better’ as the best and ‘much worse’ as the worst. The difference in mean score between the preoperative score and the 2-year follow-up score is the primary value of interest.

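### The Discussion lets the lateralized glenosphere be adopted with no further testing if no infection cost is seen, but about 61 patients per arm cannot support that infection condition

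*Protocol article*

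**What the plan says.** The adoption statement is in the Discussion of the protocol article, in the paragraph that places the trial within the safe introduction of a new surgical product: "If it finds an advantage without infection as an expense, it can be implemented in the treatment of patients without further testing". It sets two conditions, that an advantage is found and that infection is not its price. The next sentence adds that treatment will be followed through the national shoulder arthroplasty registry.

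Elsewhere, infection appears as one item in the list under Secondary functional outcomes: "surgical complications (nerve damage, fracture, infection, instability, disposition of component and dislocation) will be noted". The article gives no expected infection rate and names no test for infection.

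The two sample size sections concern other endpoints. One is for MTPM at 2 years (22 per group, 56 in total). The other is for WOOS, which sets the trial size: "48 patients are needed in each group resulting in a study population with 122 participants". The design is a "investigator initiated, single-centre, 1:1 randomized controlled trial". The Follow-up section also plans complication and revision data from records and the hospital database after 10 years.

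**The concern.** Infection is the only harm that the adoption sentence names. Meeting that condition, together with an advantage, is what would make further testing unnecessary. An advantage in function or migration carries no information about infection, so the condition has to be judged on the infection counts alone. In a trial sized for a continuous score and a continuous migration measure, those counts will be small, and an unremarkable comparison is likely even if the true rate is considerably higher with the new component.

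At stake is what can be claimed afterwards. A non-significant infection comparison could be cited as satisfying a condition published in advance, and further testing waived on that basis, when the data are compatible with a several-fold increase. An analysis plan could define how infection is analysed, but it could not make 61 patients per arm informative enough for this use.

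**Working it through.** **Inputs from the protocol article**
- WOOS (section Sample size calculation WOOS): SD 15 points, difference to detect 10 points, alpha 5%, power 90%, and 20% allowed for loss of patients.
- Allocation 1:1, 122 patients in total.

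**The plan's own figure.** The normal-approximation formula, taken as two-sided, gives n per group = 2 × (1.960 + 1.282)² × (15/10)² = 47.3, rounded up to 48. Allowing for 20% drop-out, 48/0.8 = 60 per group, or 120 in total, within two patients of the stated 122. The trial size is therefore explained by WOOS alone. At 1:1, 122/2 = 61 per arm, with about 48 completers per arm if drop-out is as planned.

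**Assumptions.** The documents give no infection rate, so control rates of 1%, 2%, 3% and 5% are assumed. They name no test, so a two-sided 5% Fisher test is used first, then two alternatives.

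**Reading 1: no significant excess (Fisher).** Power is the sum, over all pairs of counts that reach p ≤ 0.05 in the direction of more infections with the lateralized component, of Bin(x; 61, control rate) × Bin(y; 61, lateralized rate).

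| Control rate | Power, doubled | Missed | Power, tripled | Missed | Power, tripled, 48 per arm |
|---|---|---|---|---|---|
| 1% | 0.1% | 99.9% | 0.6% | 99.4% | 0.2% |
| 2% | 1.1% | 98.9% | 5.7% | 94% | 2.8% |
| 3% | 3.4% | 97% | 14% | 86% | 8.5% |
| 5% | 9.0% | 91% | 33% | 67% | 23% |

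With no infections in the control arm, 5 in the other arm give p = 0.057 and 6 give p = 0.027. Significance thus needs at least 6 v 0, and likewise 8 v 1 or 10 v 2.

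**Sensitivity to the test.** Fisher's test is conservative with sparse counts. The normal approximation gives power for a tripled rate of 12%, 20%, 28% and 45% at the same control rates, so 88%, 80%, 72% and 55% are missed. For 80% power on that approximation, a tripled rate would need 769, 376, 245 and 141 patients per arm.

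**Reading 2: no more infections than control.** The probability that the lateralized count is at or below the control count, 61 per arm:

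| Control rate | No true difference | Rate doubled |
|---|---|---|
| 1% | 71% | 49% |
| 2% | 64% | 36% |
| 3% | 61% | 28% |
| 5% | 58% | 19% |

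**Best case.** If the lateralized arm has no infections, the exact two-sided 95% upper limit is 1 − 0.025^(1/61) = 5.9%. With 48 patients it is 1 − 0.025^(1/48) = 7.4%.

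**The case against.** The sentence is one permissive remark in the Discussion, with no test, threshold or decision-maker, and the Statistics section contains no such rule. It also requires an advantage. Read in sequence, the article describes manufacturer testing, then this trial, then registry control, so the waiver may mean only that no further trial is needed before use. Low power for a rare complication is common to trials of this size, and the harm the article itself worries about is loosening; nothing in it suggests that lateralization raises infection. The lack of an infection margin could be left to an analysis plan.

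Much of this stands and limits the point. The sentence should not be called a decision rule, and a missing margin is not the complaint. The registry and 10-year data are real safeguards, but they largely act after adoption, so they do not support waiving testing beforehand. Low power would not matter if the article merely recorded infections; it matters because the article makes the absence of an infection cost a condition for adoption.

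Two stronger readings are tempting and are not supported. A reader might infer that a tripled rate would nearly always go undetected. With Fisher's test that holds only for control rates of about 2% or below: at 5% a third of trials would detect it, at 10% about 74%, and the documents give no rate. A reader might also infer that the condition cannot separate a safe implant from an unsafe one at all. A simple count comparison does discriminate, though weakly.

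**Conclusion.** The concern holds in a limited form. The Discussion states an adoption condition on infection that a trial of 61 per arm, sized for WOOS and MTPM, cannot support. For assumed control rates of 1% to 5%, a two-sided Fisher test misses a tripled rate in 67% to 99% of trials and a doubled rate in 91% or more. Judged by counts alone, the condition is met in 58% to 71% of trials with no difference and in 19% to 49% when the rate doubles.

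These figures rest on assumed infection rates and an assumed way of judging infection, since the article states neither. The conclusion does not depend on the choice: under the normal approximation at 5%, the most favourable case shown for a tripled rate within that range, more than half of trials (55%) would still miss it. No primary analysis, estimate or sample size is affected. What needs correcting is the claim.

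**What to change.** In the Discussion:
1. Delete the waiver of further testing, the last three words of the adoption sentence.
2. State that infection and the other complications will be reported per arm, with an exact 95% confidence interval for the difference.
3. State that a non-significant or absent difference will not be read as showing no infection cost, because 122 patients cannot exclude a several-fold increase.
4. State that any conclusion on infection is provisional pending the registry surveillance and the 10-year complication data already planned.

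The cost is a change of wording and confidence intervals from data already collected. Sample size and conduct do not change. The downside is a more modest adoption claim.

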### Trial status

Version 1.1, May 18, 2022

Start inclusion: August 1, 2022

Finish date of recruitment to the first part of the study: July 31, 2023

Finish date of recruitment of all 122 patients: July 31, 2024

Finish date of follow-up for the first part of the study: July 31, 2025

Finish date of follow-up for all 122 patients: July 31, 2026

## Data Availability

The electronic data will be stored in closed drives and printed data will be stored in closed cabinets. The datasets used and/or analysed during the current study are available from the corresponding authors on reasonable request. The study has been notified to Pactius and has approval number P-2021-231.

## Abbreviations

ROM: Range of motion
PROM: Passive range of motion
ASA: American Society of Anaesthesiology
OSS: Oxford Shoulder Score
WOOS score: Western Ontario Osteoarthritis of the Shoulder index
VAS score: Visual analogue scale
DXA: Duel energy x-ray absorptiometry
BMD: Bone mineral density
REdCap: Research Electronic data Capture
MB-RSA: Model-based radiostereometric analysis
CAD models: Computer-aided design models
MTPM: Maximum total point motion
QALY: Quality-adjusted life years
SD: Standard deviation
